## **4 ADVERSE EVENT MANAGEMENT**

### **4.1 Definitions**

#### **4.1.1 Adverse Events (AE)**

An Adverse Event (AE) is defined as any untoward medical occurrence in a trial participant and which does not necessarily have a causal relationship with the treatment/intervention. Only AEs clearly related to the use of CPAP or HFNO or expected will be recorded.

The following are expected adverse events and will be recorded in the CRF; they predominantly relate to the use of CPAP, as there are minimal AEs reported for HFNO:

- Interface intolerance due to excessive air leaks
- Pain
- Cutaneous pressure sore or pressure area
- Claustrophobia
- Oro-nasal dryness
- Respiratory acidosis with pH <7.25 prior to intubation
- Haemodynamic instability
- Vomiting
- Aspiration of gastric contents

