### **2.10.3 Standard care**

Standard care will comprise regular ward level oxygen therapy according to local protocol/guidelines, and excludes escalation to CPAP and HFNO. Administration of regular oxygen therapy will not be protocolised and left to clinical discretion for management.

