## **2.11 Blinding and contamination**

### **2.11.1 Methods for ensuring blinding**

This is an open-label study. However, while the study is in progress, access to tabular results by treatment allocation will not be available to the research team, patients, or members of the Trial Steering Committee (unless the Data Safety Committee advises otherwise).

In addition, the clinical staff delivering the interventions will not be blinded or masked, and therefore there is possibility that bias could be introduced by knowledge of treatment allocation through administration of interventions. Due to the exceptional circumstance of this study, it is not possible to protocolise the interventions or provide training for clinical staff to ensure that delivery of the treatment is standardised across the trial sites. We will assess this bias in the interim stages of the trial and present the trial data by each site and intervention to the Data Monitoring

Committee and Trial Steering Committee. Both our primary and secondary outcomes are objective and this will ensure that detection bias is reduced.

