### 2.11.2 Contamination

It is likely that the intervention the patient is randomised to may not be the one that is allocated or the patient may have crossed over to one of the other interventions. In this case, we will still include the patient in the trial on an intention-to-treat basis. However, we will do additional statistical analyses which will accommodate for patients who did not conform to the allocated intervention by means of a compliers analysis (as detailed in the statistical analysis section).

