### 4.1.3 Assessing and Reporting AEs, SAEs and related SAEs

#### Adverse events

These events will be included as part of the safety analysis for the trial and do not need to be reported separately to the Trial Coordinating Centre. The local PI will be responsible for confirming the relatedness of any AE to the trial intervention. If an AE occurs, the clinician responsible for the patient should decide whether it is safe to continue CPAP, with or without modification, or whether CPAP should be discontinued. AEs will be reviewed/monitored by the TMG for trends.

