#### Serious adverse events

Serious adverse events (SAE), occurring from the time of randomisation until 30 days post cessation of the trial intervention must be recorded on the Serious Adverse Event reporting form in the participant's CRF and emailed to WCTU ([[contact]](mailto:[contact])) within 24 hours of the research staff becoming aware of them. Events that do not need reporting as SAEs are listed below.

For each SAE the following information will be collected from the investigator site:

- full details in medical terms and case description
- event duration (start and end dates, if applicable)
- action taken
- outcome
- seriousness criteria
- causality (i.e. relatedness to intervention), in the opinion of the investigator (Table 3)

Once received, an independent causality assessment will be undertaken by the CI or clinical delegate. For any SAEs which are suspected to be caused by the trial intervention by either the CI or site clinician, expectedness will be confirmed by the CI or a delegate at WCTU. SAEs that are deemed to be unexpected and related to the study will be notified to the Research Ethics Committee (REC) within 15 days. All such events will be reported to the Sponsor, Trial Steering Committee and Data Monitoring Committee at their next meetings. All participants experiencing SAEs will be followed-up until the event has been resolved or a final outcome has been reached as per protocol until the end of the trial.

**Table 3.** Relationship of SAEs to trial intervention

| Relationship to trial intervention | Description                                                              |
|------------------------------------|--------------------------------------------------------------------------|
| Unrelated                          | There is no evidence of any causal relationship                          |
| Unlikely to be related             | There is little evidence to suggest there is a causal relationship (e.g. |

|                       |                                                                                                                                                                                                                                                                                                                                                                     |

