#### **4.1.4 SAEs Exempt from reporting**

Because the trial is recruiting a population that is already in a life-threatening situation, it is expected that many of the participants will experience SAEs. Events that commonly occur in this population and those that are collected as outcomes of the trial should not be reported as SAEs. Common events, not for reporting include:

- Death
- Organ failure
- Pneumonia
- Intubation
- Tracheostomy

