## **5 DATA MANAGEMENT**

### **5.1 Data collection and management**

We will use the standard CTU study web-based application for study management and to record participant data (including case report forms) in accordance with the protocol. Clinical data will be collected during the ICU stay up to 30 days after randomisation or hospital discharge, whichever is later. Baseline characteristics collected include patient demographics, comorbidities, pre-admission function, inclusion/exclusion criteria, consent, time and date of randomisation, temperature at hospital admission, and COVID-19 diagnosis status. Data captured following randomisation will include initial device settings, duration of ventilation, prone therapy, ICU/hospital admission status, patient observations, AEs (treatment failure, need for other treatments, renal function, renal replacement therapy), survival status. Confirmation of COVID-19 diagnosis at any point will be recorded. Ethnicity, socioeconomic status and mortality will be reported from hospital records up until discharge and tracked after discharge using NHS Digital, the ICNARC and Research Centre and equivalent NHS data linkage in the devolved nations. ICU and hospital length of stay will be obtained from local centres or data linkage if appropriate.

The case report form (CRF) has been developed by the CTU and made available to the participating sites as a paper and electronic CRF (eCRF) for ease of data collection; supporting materials will be available to staff. All documents will be stored safely in confidential conditions. On all trial-specific documents, other than the signed consent, the participant will be referred to by a unique trial-specific number/patient identifier/code in any database, not by name. The trial will be conducted in accordance with the current approved protocol, Good Clinical Practice (GCP), relevant data protection regulations and standard operating procedures (SOPs). A monitoring plan and risk assessment will be devised to protect participant safety and integrity of trial data.

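### Protocol sections 4.1.1 and 5.1 disagree on which adverse events are recorded, and the 4.1.1 rule gives unlisted events a route to the record that standard-care patients who keep to allocation do not have

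*Protocol*

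**What the plan says.** Section 2.4.2 names adverse events and serious adverse events as the safety data. Section 4.1.1 defines an AE broadly, without requiring a causal link, and then narrows what is kept: "Only AEs clearly related to the use of CPAP or HFNO or expected will be recorded". Nine expected events follow: interface intolerance, pain, pressure sore or area, claustrophobia, oro-nasal dryness, respiratory acidosis before intubation, haemodynamic instability, vomiting and aspiration.

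Section 5.1 lists what is captured after randomisation and includes "AEs (treatment failure, need for other treatments, renal function, renal replacement therapy", with no condition on relatedness or arm.

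Other sections that bear on the point:

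- 4.1.3, on AEs: "These events will be included as part of the safety analysis for the trial". The local PI confirms relatedness.
- 4.1.3, on SAEs: "Serious adverse events (SAE), occurring from the time of randomisation until 30 days post cessation of the trial intervention must be recorded". This does not depend on relatedness.
- 4.1.4: "Events that commonly occur in this population and those that are collected as outcomes of the trial should not be reported as SAEs". The examples are death, organ failure, pneumonia, intubation and tracheostomy.
- 2.10.3: standard care "excludes escalation to CPAP and HFNO".
- 2.11.1: "the clinical staff delivering the interventions will not be blinded or masked".
- 2.11.2: crossover is foreseen, in that "the patient may have crossed over to one of the other interventions".

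**The concern.** There are two linked problems.

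First, the protocol gives two answers to the question of which AEs go on record. Under 4.1.1 the four items in 5.1 would be kept only if clearly due to a device. Under 5.1 they are kept unconditionally. Both cannot be right.

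Second, the 4.1.1 rule makes recording depend on exposure. An event that is not on the list enters the record only through its link to CPAP or HFNO. Patients allocated to a device can satisfy that; patients on standard care who stay on it cannot. The link is judged by staff who know the allocation. Section 2.11.1 relies on the objectivity of the primary and secondary outcomes to limit detection bias, and a relatedness-gated AE lacks that protection.

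At stake is the safety comparison for this class of event. If the arms are compared, the standard-care count is zero by rule among adherent patients, so a device can look equal or worse but never better. If they are not compared, these harms have no control group. An analysis plan cannot repair this, because events that were not recorded cannot be recovered.

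**Working it through.** The protocol gives no figure for AE rates, so there is nothing to reproduce. The check is a comparison of lists and of routes to the record, followed by an illustration on assumed inputs.

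**Step 1: overlap of the lists.** Section 4.1.1 has 9 expected events and 5.1 names 4 AEs. Taking the four in turn, none appears among the nine. Overlap: 0 of 4.

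**Step 2: routes to the record under 4.1.1, 4.1.3 and 4.1.4.**

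| Event | CPAP or HFNO arm | Standard care, as allocated |
|---|---|---|
| One of the nine listed | recorded | recorded |
| SAE, not exempt | recorded | recorded |
| Unlisted, non-serious | recorded if judged clearly device-related | no route |
| Unlisted, SAE-exempt, not an outcome | recorded if judged clearly device-related | no route |

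The last row is found by subtraction. The exempt examples are 5 (death, organ failure, pneumonia, intubation, tracheostomy). Death and intubation are outcomes in 2.4.1, and none of the other three is on the list of nine, so 5 − 2 = 3 remain. Section 5.1, if it prevails, restores its own four items in all arms and hence the renal part of organ failure.

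**Step 3: direction of the bias.** Let u be the true risk of an unlisted event in the device arm and m the share of such events judged clearly device-related. With n = 1,334 per arm (section 6.1):

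- expected recorded count, device arm = n × u × m
- recorded count, standard care without crossover = 0, whatever the true risk.

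The protocol gives neither u nor m. Over an assumed range:

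- u = 5%, m = 2%: 1,334 × 0.05 × 0.02 = 1.3 against 0
- u = 8%, m = 5%: 1,334 × 0.08 × 0.05 = 5.3 against 0
- u = 8%, m = 10%: 10.7 against 0
- u = 8%, m = 20%: 21.3 against 0.

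If the true standard-care risk were 10%, the true counts would be 1,334 × 0.08 = 107 and 1,334 × 0.10 = 133. The recorded difference would then run the opposite way to the true one.

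**Step 4: crossover.** Suppose a share c of the standard-care arm receives a device, a share d of the device arm does, and there is no true difference. The recorded risk ratio is (d × u × m)/(c × u × m) = d/c. With d = 1 it is 20, 10, 5 and 3.3 at c = 5%, 10%, 20% and 30%; with d = 0.8 it is 16, 8, 4 and 2.7. Here c and d are again assumptions, and m now stands for background events attributed to a device. Crossover weakens the distortion but does not remove it.

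**The case against.** The best defence is that the 5.1 items are clinical data fields loosely labelled as AEs. Renal function is a measurement, and need for other treatments is a treatment record; both sit beside device settings and patient observations. One CRF holding the nine events and the 5.1 fields could serve both sections. That is plausible, but it requires overriding the label in 5.1 and the word that opens the restriction in 4.1.1. The protocol does neither.

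It is also fair that restricting AE collection is a deliberate choice for a pragmatic trial of treatments already in use, run by staff under extreme pressure. And an event truly caused by a device has no counterpart in patients without one, so a zero in adherent standard care partly follows from the definition. What remains is that relatedness is a judgement made unblinded, and the protocol does not say that such events will be kept out of between-arm comparisons.

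Four stronger readings are tempting and go too far:

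- *Sites would record different data depending on which section they followed.* The CRF and the database are built centrally (5.1, 5.2) and forms are checked for completeness (7.7), so divergence between sites is conjecture.
- *The safety data as a whole are biased.* Only the residual category is touched. Haemodynamic instability and respiratory acidosis are among the nine, and intubation and duration of invasive ventilation are outcomes, so parts of organ failure are captured in all arms.
- *The rule will produce a false significant harm.* Six events against none would give a two-sided Fisher p of about 2 × (1/2)^6 = 0.031. But the protocol specifies no such test, and whether six would be reached depends wholly on assumed inputs.
- *Organ failure, pneumonia and tracheostomy must be added.* Section 4.1.4 sets them aside on purpose, as events common in this population. Adding them is a preference, not the correction of an error.

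**Conclusion.** The contradiction is established on the text: nine events in one section, four others in the next, no overlap and no rule of precedence. The asymmetry is also established. For unlisted AEs that are non-serious or SAE-exempt, 4.1.1 opens a route to the record for device patients, on unblinded judgement, and none for standard-care patients who keep to allocation. Any between-arm comparison of those events is therefore biased by the recording rule.

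The direction is known: against the devices, or neutral. The size is not known. It depends on true risk, the share judged clearly related, crossover and device uptake, and the protocol gives none of these. On assumed values the recorded imbalance runs from about 1 against 0 to about 21 against 0, so it may be negligible. The nine listed events, non-exempt SAEs, the primary outcome and the stopping rules are not affected. This should be corrected, but it does not threaten the trial's main conclusion.

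**What to change.** Make 4.1.1 the single AE list: the nine expected events plus the four items now in 5.1, recorded in all three arms whatever the cause. Let 5.1 refer to that list and not carry its own. State that any other AE recorded as clearly related to CPAP or HFNO will only be described for device-treated patients and will not be compared with standard care.

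Adding organ failure, pneumonia and tracheostomy is optional. It would give these events a control group, at the price of up to three more CRF tick boxes.

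The cost of the main change is rewording two sections. The four 5.1 items are already meant to be captured, so there are no extra patients or visits. The drawback is that many of these events will come from COVID-19 itself, so the comparison will be noisy.

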#### **4.1.2 Serious Adverse Events (SAEs)**

A Serious Adverse Event (SAE) is an AE that fulfils one or more of the following criteria:

- Results in death
- Is immediately life-threatening
- Requires hospitalisation or prolongation of existing hospitalisation
- Results in persistent or significant disability or incapacity
- Is a congenital abnormality or birth defect
- Immediate intervention was required to prevent one of the above or is an important medical condition.

### 4.1.3 Assessing and Reporting AEs, SAEs and related SAEs

#### Adverse events

These events will be included as part of the safety analysis for the trial and do not need to be reported separately to the Trial Coordinating Centre. The local PI will be responsible for confirming the relatedness of any AE to the trial intervention. If an AE occurs, the clinician responsible for the patient should decide whether it is safe to continue CPAP, with or without modification, or whether CPAP should be discontinued. AEs will be reviewed/monitored by the TMG for trends.

#### Serious adverse events

Serious adverse events (SAE), occurring from the time of randomisation until 30 days post cessation of the trial intervention must be recorded on the Serious Adverse Event reporting form in the participant's CRF and emailed to WCTU ([[contact]](mailto:[contact])) within 24 hours of the research staff becoming aware of them. Events that do not need reporting as SAEs are listed below.

For each SAE the following information will be collected from the investigator site:

- full details in medical terms and case description
- event duration (start and end dates, if applicable)
- action taken
- outcome
- seriousness criteria
- causality (i.e. relatedness to intervention), in the opinion of the investigator (Table 3)

Once received, an independent causality assessment will be undertaken by the CI or clinical delegate. For any SAEs which are suspected to be caused by the trial intervention by either the CI or site clinician, expectedness will be confirmed by the CI or a delegate at WCTU. SAEs that are deemed to be unexpected and related to the study will be notified to the Research Ethics Committee (REC) within 15 days. All such events will be reported to the Sponsor, Trial Steering Committee and Data Monitoring Committee at their next meetings. All participants experiencing SAEs will be followed-up until the event has been resolved or a final outcome has been reached as per protocol until the end of the trial.

**Table 3.** Relationship of SAEs to trial intervention

| Relationship to trial intervention | Description                                                              |
|------------------------------------|--------------------------------------------------------------------------|
| Unrelated                          | There is no evidence of any causal relationship                          |
| Unlikely to be related             | There is little evidence to suggest there is a causal relationship (e.g. |

|                       |                                                                                                                                                                                                                                                                                                                                                                     |
|-----------------------|---------------------------------------------------------------------------------------------------------------------------------------------------------------------------------------------------------------------------------------------------------------------------------------------------------------------------------------------------------------------|
|                       | the event did not occur within a reasonable time after administration of the trial intervention or device). There is another reasonable explanation for the event (e.g. the patient's clinical condition, other concomitant treatment).                                                                                                                             |
| Possible relationship | There is some evidence to suggest a causal relationship (e.g. because the event occurs within a reasonable time after administration of the trial intervention or device). However, the influence of other factors may have contributed to the event (e.g. the patient's clinical condition, other concomitant treatments). This event will be reported as related. |
| Probable relationship | There is evidence to suggest a causal relationship and the influence of other factors is unlikely. This event will be reported as related.                                                                                                                                                                                                                          |
| Definitely related    | There is clear evidence to suggest a causal relationship and other possible contributing factors can be ruled out. This event will be reported as related.                                                                                                                                                                                                          |

#### **4.1.4 SAEs Exempt from reporting**

Because the trial is recruiting a population that is already in a life-threatening situation, it is expected that many of the participants will experience SAEs. Events that commonly occur in this population and those that are collected as outcomes of the trial should not be reported as SAEs. Common events, not for reporting include:

- Death
- Organ failure
- Pneumonia
- Intubation
- Tracheostomy

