## 3 METHODS AND ASSESSMENTS

### 3.1 Schedule of delivery of intervention and data collection

**Table 2.** Trial assessments

| Visit                                      | 1                 | 2                                                   | 3                                      | 4                                  |
|--------------------------------------------|-------------------|-----------------------------------------------------|----------------------------------------|------------------------------------|
| Visit Window
(No. Weeks $\pm$ No. Days) | Day 0
Baseline | Regular in-hospital
reviews
(at least weekly) | Day 30
( $\pm$ 2 days) † | Hospital
discharge † |
| Baseline data collection                   | ✓                 |                                                     |                                        |                                    |
| Randomisation                              | ✓                 |                                                     |                                        |                                    |
| Intervention                               | ✓*                | ✓*                                                  |                                        |                                    |
| Adverse events                             |                   | ✓                                                   | ✓                                      | ✓                                  |
| Survival status                            |                   | ✓                                                   | ✓                                      | ✓                                  |
| Outcome assessment                         |                   |                                                     | ✓                                      | ✓                                  |

\*- Intervention will be delivered up to point of death, tracheal intubation, or clinical determination that no ongoing need (palliation or improvement).

†- Participants to be followed-up to day 30 or hospital discharge, whichever comes later

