### **4.3 Notification of deaths**

Death is collected as a study outcome. No separate notification of death is required.

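### The SAE exemption has no exception for events suspected to be device-related, and the SAE window varies with treatment length

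*Protocol*

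**What the plan says.** **Exemption.** Protocol Section 4.1.4 rules that "Events that commonly occur in this population and those that are collected as outcomes of the trial should not be reported as SAEs". Under "Common events, not for reporting include" it names death, organ failure, pneumonia, intubation and tracheostomy. Section 4.3 adds for deaths: "No separate notification of death is required". Neither section sets out a different rule for an event that the investigator attributes to the device.

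**Expedited route.** Under Section 4.1.3 the site sends in an SAE form. A central causality assessment follows receipt, then an expectedness assessment if relatedness is suspected. "SAEs that are deemed to be unexpected and related to the study will be notified to the Research Ethics Committee", with a 15-day limit.

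**SAE window.** The same section requires reporting of SAEs "occurring from the time of randomisation until 30 days post cessation of the trial intervention must be recorded". The footnotes to Table 2 (Section 3.1) end the intervention at death, intubation or a judgement that it is no longer needed, and say: "Participants to be followed-up to day 30 or hospital discharge, whichever comes later".

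**Non-serious events.** Section 4.1.1 says: "Only AEs clearly related to the use of CPAP or HFNO or expected will be recorded". Nine expected events follow, and "they predominantly relate to the use of CPAP, as there are minimal AEs reported for HFNO". Section 5.1 gives a different set of AE items, covering treatment failure, other treatments needed, and renal function and replacement.

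**The concern.** Not reporting common events and trial outcomes as SAEs is ordinary practice in a critically ill population. The usual companion to such a rule is an exception for a case that the investigator thinks the intervention caused, and that exception is absent here. The most serious harms a respiratory device could do (a death, a pneumonia after aspiration, organ failure) are the ones with no written route to case-by-case review. Section 4.2 gives the sponsor the duty of expedited reporting of related and unexpected SAEs, which it cannot carry out for events it is never sent.

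Two further rules bear on whether the remaining safety data can be compared between arms. The SAE window is tied to when treatment stops, not to randomisation, so patients are observed for different lengths of time. The filter on unlisted AEs refers to CPAP and HFNO, which standard care excludes (Section 2.10.3).

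**Working it through.** The plan gives no figure to reproduce here. The check sets the sections side by side; the only arithmetic concerns the window.

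**1. What happens to an exempt event suspected to be device-related**

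| Event | SAE report (4.1.4, 4.3) | Causality, expectedness and 15-day steps (4.1.3) | Captured elsewhere |
|---|---|---|---|
| Death | No | Not reached | Yes: primary outcome (2.4.1) |
| Intubation | No | Not reached | Yes: primary outcome (2.4.1) |
| Renal failure | No | Not reached | Partly: renal items (5.1) |
| Pneumonia | No | Not reached | Not an outcome, not a named follow-up item |
| Other organ failure | No | Not reached | Not an outcome, not a named follow-up item |

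Aspiration of gastric contents is a listed AE in Section 4.1.1, but a pneumonia that follows it is exempt.

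**2. The SAE window**

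With T days of treatment, the window closes on day T + 30 after randomisation.

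- T = 1: day 31
- T = 12: day 42
- T = 20: day 50
- T = 30 (the treatment duration in the Trial Summary): day 60

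Table 2 follow-up ends at day 30, or at discharge if that is later. A patient treated for 12 days and discharged before day 42 has an SAE window that outlasts follow-up. T is itself shaped by the outcome: a patient intubated on day 2 who survives is observed to day 32, while one who stays on the device for 12 days is observed to day 42.

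**3. Illustration of unequal windows**

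The protocol gives neither an SAE rate nor treatment lengths by arm, so both are assumed. With a constant daily rate r, the proportion with an SAE is 1 − exp(−r × (T + 30)). For r = 0.005:

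- T = 3: 1 − exp(−0.165) = 15.2%
- T = 10: 1 − exp(−0.200) = 18.1%

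The gap is 2.9 points although the daily risk is identical. The table gives both proportions and, in brackets, the chance that a two-sided 5% comparison at 1334 per arm (Section 6.1) would call the gap significant.

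| r per day | T = 3 v 6 | T = 3 v 10 | T = 5 v 15 | Fixed to day 30 |
|---|---|---|---|---|
| 0.002 | 6.4% v 7.0% (8%) | 6.4% v 7.7% (26%) | 6.8% v 8.6% (43%) | 5.8% both |
| 0.005 | 15.2% v 16.5% (14%) | 15.2% v 18.1% (52%) | 16.1% v 20.2% (78%) | 13.9% both |
| 0.01 | 28.1% v 30.2% (23%) | 28.1% v 33.0% (78%) | 29.5% v 36.2% (96%) | 25.9% both |

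These figures ignore death as a competing risk and show direction only.

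**4. The relatedness filter**

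The nine listed events carry no arm restriction. An unlisted event must be clearly related to CPAP or HFNO, so under standard care it can hardly qualify without crossover. The SAE sentence in Section 4.1.3 has no such filter, and Table 3 includes an unrelated category, so the filter is best read as applying to non-serious events. The wording is still loose: Section 4.1.2 defines an SAE as a kind of AE, and Table 3 treats even a possible relationship as related, whereas Section 4.1.1 asks for a clear one.

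**The case against.** The strongest reply is that the harms that matter most are not lost. Death and intubation form the primary composite, analysed by intention to treat (Section 6.2.4), with survival status supported by data linkage. The DMC sees interim outcome reports and unblinded safety data (Sections 7.10 and 4.2). This stands. A reader might infer that deaths are missed or cannot be compared between arms; the documents do not support that.

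A reader might also infer that an arm could be dropped on distorted SAE counts, since Section 2.2 mentions evidence of harm. Section 6.1 bases the formal criteria on the primary outcome, so that argument does not hold for the formal rule. The SAE data still inform the DMC's general safety advice.

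Other routes to the ethics committee exist: urgent safety measures (Section 4.4) and annual reports (Section 7.2). The 15-day route also requires an event to be unexpected, and a pneumonia after aspiration might not meet that test. Both points stand, but neither replaces a causality assessment of the individual case.

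Exempting common events is a reasoned choice, and the fact that pneumonia is not an outcome does not contradict it. This too stands; the defect is the missing exception, not the exemption. Nor does the 25% day-28 mortality quoted in Section 6.1 measure the problem: it is all-cause mortality on standard care in a drug trial and says nothing about device-related deaths.

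On the window, no treatment lengths by arm are given, so an imbalance between arms is possible but not shown. The Trial Monitoring Plan and the DMC charter may add operational detail, but they are not at hand and would not change what Sections 4.1.3 and 4.1.4 tell sites to do.

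**Conclusion.** The point holds in three parts of unequal weight.

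1. **Exemption.** As written, a death, organ failure, pneumonia, intubation or tracheostomy suspected to be device-related never enters the causality, expectedness and 15-day steps. For death and intubation the loss is confined to individual review and expedited reporting. It is larger for pneumonia and non-renal organ failure, which have no other named place in the data. This rests on the text alone.
2. **Window.** The SAE window and Table 2 follow-up do not match. The window varies by patient, from about 30 days up to 60 days on the 30-day treatment duration in the Trial Summary. Raw SAE proportions can therefore cover unequal observation time. How far this biases a comparison between arms depends on treatment lengths and SAE rates that the protocol does not give.
3. **AE filter.** Unlisted non-serious AEs are structurally under-recorded under standard care. Non-exempt SAEs and the nine listed events are not affected.

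The plan should be changed, but the primary comparison is not at risk.

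**What to change.** 1. In Sections 4.1.4 and 4.3, keep the exemption but add: unless the investigator suspects a relation to the trial intervention, in which case the event is reported under Section 4.1.3.
2. Reconcile the SAE window in Section 4.1.3 with Table 2. Compare SAEs between arms over one fixed window from randomisation, for example to day 30, and keep later related SAEs as additional reports. A window to day 30 or discharge would not be enough for the comparison, because discharge also varies by patient and length of stay is itself an outcome.
3. In Section 4.1.1, state that the named AE list is recorded in all three arms regardless of attribution, and base between-arm AE comparisons on that list. Reconcile the list with Section 5.1, and make clear that the relatedness filter does not apply to SAEs.

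The cost is protocol and CRF wording and a few more SAE forms. The exemption for events not suspected to be related stays, so the reporting load on sites changes little.
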